## Abstract

Spatial navigation (SN) has been reported to be one of the first cognitive domains to be affected in Alzheimer’s disease (AD), which occurs as a result of progressive neuropathology involving specific brain areas. Moreover, the epsilon 4 isoform of apolipoprotein-E (APOE-ε4) has been associated with both sporadic and familial late-onset AD, and patients with mild cognitive impairment (MCI) due to AD are more likely to progressively deteriorate. Spatial navigation performance will be examined on a sample of 76 community-dwelling senior citizens (25 healthy controls; 25 individuals with subjective cognitive decline (SCD); and 26 patients with MCI due to AD) via a virtual computer-based task (i.e., the AppleGame) and a naturalistic task (i.e., the Detour Navigation Test—modified version) for which a wearable device with sensors will be used for recording gait data and revealing physiological parameters that may be associated with spatial disorientation. We expect that patients with MCI due to AD and APOE-ε4 carriers will show altered SN performances compared to individuals with SCD and healthy controls in the experimental tasks, and that VR testing may predict ecological performance. Impaired SN performances in people at increased risk of developing AD may inform future cognitive rehabilitation protocols for counteracting spatial disorientation that may occur during elders’ traveling to unfamiliar locations. The research protocol has been approved by the Ethics Committee of the Istituto Auxologico Italiano. Findings will be published in peer-reviewed medical journals and discussed in national and international congresses.

## 1. Introduction

### 1.1. Spatial Navigation Processes

Navigation abilities include the precision at which spatial information is encoded from sensory experiences, the ability to build up spatial representations of external environments, and the efficacy by which they are used to guide navigational behavior. These abilities are highly interdependent, and typical navigational tasks bridge multiple levels [1]. Navigation in space is a complex ability including multiple cognitive and perceptual processes that are essential for the autonomy of individuals in their lives [2]. Specifically, spatial navigation (SN) can be defined as the ability of a human being to use multiple cues to plan and travel a route [3]. Cues that are fundamental for SN can be basically divided as follows: (i) self-motion ones, usually referred to idiothetic cues; and (ii) environmental ones, also known as allothetic cues. The former includes motor, vestibular information, and proprioceptive information used to track one’s self position and orientation; the latter comprises environmental (visual predominantly) information pertaining to stable space cues, such as landmarks and boundaries, that are used to estimate one’s position and orientation within the environment [4]. Crucially, both idiothetic and allothetic cues can inform and support spatial frames of reference. The first frame of reference is the egocentric representation, which is a body-dependent representation of the space; the second frame of reference is the allocentric representation, which is a body-independent (world-centered) representation of the environment [5] (Figure 1).

The human navigation system naturally encourages the strategic translation of egocentric and allocentric information and the use of path integration. People ordinarily use egocentric navigation strategies during visual–spatial tasks such as walking a familiar route many times [6]. The egocentric navigation strategy is self-centered and involves the encoding of spatial information in relation to the position of the navigator. It is also based on different cues, allowing individuals to navigate as follows: perpetual processing of visual landmarks by bodily movements (e.g., “Turn left at the church”, “Turn right at the supermarket”, and then “Go straight to the pharmacy”), an endogenous integration of sensorimotor stimulation, vestibular information, and self-motion [6]. By contrast, when people travel a novel route, egocentric spatial representations are not available, and world-related navigational strategies are employed (i.e., allocentric navigation). They allow individuals to mentally represent a “cognitive map” of the environment based on the relationships among landmarks. This navigation strategy is also referred to as “wayfinding” [7]. Remarkably, they permit the travelling of alternative routes to come back to the starting point [6]. Further, when people are able to use urban environmental landmarks, they can successfully navigate thanks to the translation of spatial information from allocentric to egocentric strategies and vice versa (e.g., “I am 20 m from the pharmacy” and “The pharmacy is to the right of the supermarket”) (cf., [6]). Path integration, which is based on idiothetic cues, is the ability to transform internal information into a sense of location and orientation [8]. Self-motion cues (vestibular, proprioceptive, and motor information) are combined together to allow individuals to continuously estimate their position and orientation in space [9]. When participants walk blindfolded and with ear plugs, or when the environmental information is removed (with the exception of the optic flow alone), for example, in virtual reality tasks, it is possible to isolate idiothetic information from allothetic information [10]. Allothetic navigation, in turn, uses landmarks and boundaries to successfully navigate the environment [11], and pure allothetic navigation can be detected through desktop-based virtual reality tasks only [12]. Pure path integration (PPI) is particularly important because it permits the estimation of distances and the navigation of environments without using boundaries and landmarks. PPI can be studied both in virtual tasks, providing the navigator with a scenario bare of boundaries and landmarks (Figure 2), and in real-world settings thanks to the use of idiothetic indexes, as in the case of the triangle completion task [10]. However, in our daily experience, path integration and allothetic strategies are used jointly to derive location and direction. Some studies have shown that providing allothetic information during path integration tasks or vice versa can improve people’s orientation ([8,13,14]).

Lastly, a crucial aspect during SN is represented by spatial memory, which enables individuals to encode, store, and retrieve spatial information. Pure forms of memory for spatial information like a path are recognition, free recall, directions, and symbolic representations (e.g., map drawing). Conversely, wayfinding/shortcuts and path integration tasks over complex trajectories require a balanced used of purely navigation abilities (e.g., self-motion) and spatial memory [15]. Spatial tasks used to assess spatial memory performance predominantly rely on egocentric or allocentric representation. The former may include landmark recognition and sorting or asking participants to travel a previously learned route. The latter may include map-drawing and shortcut tasks [16,17].

### 1.2. Neural Correlates of Spatial Navigation

Advances in the investigation of neural correlates of human SN have shown that a large network of cognitive mechanisms, supported by different brain areas, is involved (Figure 3). The cerebral areas sub-serving egocentric and allocentric strategies interact with specific brain cells supporting SN, i.e., head direction (HD) cells, grid cells, boundary cells, and place cells (PC). The anterodorsal thalamic nucleus—included in Papez’s circuit—contains a large proportion of head direction (HD) cells [18] informing the individual as to in which direction he/she is heading. They maximally fire when the head of the person is facing in a specific direction with respect to the surrounding environment [18]. Grid cells are neurons of the entorhinal cortex that exhibit firing fields as triangular patterns tiling the environment [19]. Boundary cells, discovered in the medial entorhinal cortex, too, fire in response to fixed boundaries in the surrounding space, contributing to analyzing the limits of the environment [20]. The hippocampal formation in both rats and humans is involved in spatial navigation [21], and spatial memories are thought to be encoded and retrieved in the hippocampus through the activity of place cells [22]. Place cells fire when an animal visits specific regions of the environment, or “place fields” [23]. Specifically, hippocampal CA1 and CA3 place cells in the medial temporal lobe provide allocentric mental representations [24]. According to Puthusseryppady [25], novel environments are first encoded as egocentric representations by the parietal cortex. As one person continues to move within the environment, the HD cells and the grid cells provide information for brain path integration. The egocentric representations are then transformed into the allocentric representations by the retrosplenial cortex and the parietal-occipital sulcus, and this is combined with information provided by the boundary cells in order to generate and store “cognitive maps” in the hippocampus via the place cells. However, in other cognitive domains, such as executive functions, attention and working memory may play a critical role in SN performance [26].

### 1.3. Spatial Navigation in Alzheimer’s Disease

AD is a multifactorial neurodegenerative disease, resulting from complex interactions between genetic and environmental factors, that remains the leading cause of dementia to date. The proportion of people aged 65 years and over is growing rapidly worldwide, and it is estimated that by 2060, this age group will account nearly for 24% to 29% of the population in Western Europe and the United States [27], representing a health emergency due to social and sanitary costs. AD is characterized by progressive deterioration of cognitive functions, with episodic memory loss and spatial disorientation as the main hallmarks. No causal therapies for AD are currently available, although drug treatment efforts are progressing [28]. Thus, advances in biomarkers and behavioral tests for identifying individuals at increased risk of developing AD represent a crucial target of current research and therapeutics. Spatial navigation, or the ability to determine and maintain a trajectory from one place to another, gradually declines in the course of physiological aging [29,30,31], and spatial disorientation (SD) represents a core feature of pathological aging, especially AD [32]. Although cognitive decline precedes overt AD, pathological changes may even begin years before there are any overt behavioral impairments, and new treatments are being sought to modify this process [33]. Indeed, it has been proposed that subjective cognitive decline (SCD) (i.e., a self-experienced decline without objective cognitive impairment) might appear at the end of the preclinical phase of AD [34]. SN complaints are frequent symptoms not only in AD but also in SCD and MCI, and can be detected by specifically designed questionnaires [35] or by virtual and real-world navigation tasks [36]. SCD is gaining increased prominence in neurodegenerative research as a potential marker for future mild cognitive impairment (MCI) due to AD [37], a condition that represents the prodromal state of dementia associated to the disease. Approximately 90% of MCI patients with pathologic cerebrospinal fluid biomarker levels at baseline develop AD within 9 to 10 years [38]. Deficits in spatial orientation appear early in the course of the AD continuum [16]. AD is mainly characterized by the presence of beta-amyloid protein plaques and neurofibrillary tangles of hyperphosphorylated tau protein. According to Laczó et al. [7], amyloid-β accumulation first emerges in the neocortical regions and, early on, affects the retrosplenial cortex, while tau pathology first emerges in the transentorhinal cortex (Braak stage I) and spreads to the posteromedial entorhinal cortex and the hippocampus (Braak stage II and III) and finally to the posterior cortical regions (Braak stage IV). Neurodegeneration and brain atrophy parallel the pattern of tau pathology spreading [39]. Degeneration of the entorhinal cortex as a critical brain district supporting SN represents an initial stage of typical AD [40], and a profound loss of its neurons occurs in very mild AD [41]. Neurofibrillary AD pathology in the entorhinal cortex and hippocampus also represent the neuropathological substrate of memory decline [42] and defective PPI [43]. Finally, tau abnormalities in the entorhinal cortex can already be observed in adults under the age of thirty [44], especially in those carrying the Apolipoprotein-E(APOE)-ε4 allele [45].

Finally, it is worth mentioning the extent to which the visual cortex modulates SN functioning. In fact, navigation is strongly driven by vision, and visuospatial deficits of cortical origin may play a critical role in AD [46]. In this neurological condition, there are a variety of visual symptoms, including visual field coverage, contrast sensitivity, color discrimination, visuospatial perception, and visual processing speed [47]. This may impair the cortical representation of visual space. Thus, as visual symptoms can occur early in AD, it is possible that the evaluation of visual cortex changes may aid in the early detection of neurodegeneration [47]. Accordingly, emerging evidence pertaining to AD neuropathology has indicated that neurofibrillary tangles and neuritic senile plaques steadily increase from the primary to associative visual cortex [47].

### 1.4. Genetic Risk Factors for Alzheimer’s Disease: Role of the Apolipoprotein-E [APOE]

Beyond increasing age, the ε4 allele of the apolipoprotein-E gene represents the most important risk factor for AD, providing an opportunity for assessing subclinical alterations of behavior at very early disease stages. APOE is centrally involved in lipoprotein metabolism and other biological functions [48]. ApoE-lipoproteins are involved in lipids transport into bloodstream, and they also bind to hydrophobic amyloid-β (Aβ) peptide, which is thought to initiate toxic events that lead to synaptic dysfunction and neurodegeneration in AD [49]. APOE genotype is determined by three main alleles, ε2, ε3 and ε4, resulting in six possible combinations (i.e., ε2/2, ε2/3, ε2/4, ε3/3, ε3/4, and ε4/4). Population frequency of the ε4 allele is approximately 14%, the ε2 allele 6%, and the ε3 allele 78% [50]. The presence of the ε4 allele is associated with an increased risk of cognitive decline during normal aging [50]. The APOE-ε4 allele is also an established risk factor for neurodegenerative conditions, such as AD [51,52] as opposed to the ε2 allele that offers protection against the disease [53,54]. Individuals carrying one APOE-ε4 allele are at threefold increased risk and those carrying two ApoE-ε4 alleles are at more than tenfold increased risk of developing AD [47]. Remarkably, cognitively normal subjects who are homozygous for the ε4 allele have reduced glucose metabolism in the same regions of the brain as in patients with probable AD [55].

In a previous investigation using a VR test (i.e., The AppleGame), we provided evidence of a specific deficit of PPI decades before potential disease onset in AD risk carriers, specifically when the recruitment of compensatory navigational strategies via supportive spatial cues from posterior cingulate/retrosplenial cortex was disabled [43].

### 1.5. Cognitive Markers Associated to AD Neuropathology

Episodic memory loss—as the most sensitive and specific cognitive marker—has long been considered “the gold standard” for the diagnosis of cognitive impairment due to AD, although its manifestation in healthy aging is quite common [56]. Early detection of incipient dementia pathophysiology is difficult during aging [6], and neuropsychologists have to schedule periodic follow-up assessments at clinics to confirm the progression of cognitive impairment and restrictions in personal and instrumental autonomy to consider a patient to have fulfilled the diagnostic criteria of dementia. Evidence from the literature indicates that SN deficits can indicate individuals at higher risk of developing AD early [29], with strong implications for timely intervention. SN deficits have the potential for early detection of cognitive alterations in topographical orientation since they have higher specificity in distinguishing AD from healthy aging [57,58], as well as from other dementia types [59,60,61]. Further, animal models of AD pathophysiology have reported on how navigation-specific brain areas are primarily affected, rather than episodic memory ones [62,63]. SN is one of the earliest cognitive domains to be impaired in patients with AD that may result in SD. It refers to instances where AD patients are unaware of where they are and are unable to reach their intended location [64]. It behaviorally manifests in AD patients making navigation errors when they go out of their community, which can lead to an increased risk of going missing in both familiar and unfamiliar environments [65], with negative consequences for personal safety, including potential injuries and, in the worst cases, even death [66]. Remarkably, incidents of the patient going missing restrict patient’s autonomy and self-efficacy and increase the caregiver’s burden [67]. In line with previous studies [64,68], AD patients may present with “moments of hesitation” while walking in their familiar environments. A “moment of hesitation” is defined as the participant slowing down/stopping and looking around to aid orientation or verbally admitting that he/she is unsure about their whereabouts. This is consistent with the fact that when participants exhibit hesitant walking, more variation would be seen in their step intervals, as compared to when they are more confident in wayfinding (cf., [25]). Further, when an elderly person loses their sense of direction, he/she moves to come back as soon as possible to reach the original start point and may present with some distressing symptoms and spatial anxiety [69], potentially influencing cardiac and respiratory physiological functions. Considering SN dysfunction as a cognitive biomarker of AD, interventions that may help in preventing SD using the most advanced wearable technology may contribute to detecting and treating the initial manifestation of the disease. SD has been specifically described in AD and MCI patients as deficits in route learning, free recall or recall of the temporal order of the landmarks, landmarks recognition and location on a 2D map, route drawing, and evaluating directions [70]. However, to date, no study in the literature has pointed out physiological correlates (e.g., physiological stress indexes) that might be associated with them. Deterioration in SN, manifested in poor hippocampus-dependent allocentric navigation, may also occur before the clinical onset of dementia [71]. A study investigating navigation skills as a function of the APOE allele found that patients with amnestic MCI and APOE-ε4-positive allele performed more poorly on both allocentric and egocentric tests than amnestic MCI patients with the APOE-ε4-negative allele [72]. Further, it has been demonstrated that virtual and ecological SN tasks can differentiate the SN performances of amyloid-positive MCI patients and amyloid-negative MCI patients ([16,73]). Finally, from the earliest stages of AD, the presence of specific impairment in the ability to encode and store an allocentric hippocampal representation and then to translate it into an egocentric parietal representation has been recently observed, and it has been proposed as a specific cognitive process that may be useful in supporting the recall of spatial scenarios too [74], which could be impaired even in premorbid AD.

### 1.6. Technological Solutions to Avoid Spatial Disorientation for Cognitively Impaired Older Adults

New technological solutions, including digital devices, sensors, and VR, represent promising means for assessment, monitoring, and intervention in AD population [75], but scientific investigations in this research field are still lacking. Advances in technology currently provide the potential for designing innovative solutions for evaluating, monitoring, and treating AD-related symptoms, both cognitive and non-cognitive ones [75]. Co-designing cutting-edge technological solutions by using brainstorming, focus groups, questionnaires, detailed interviews, and surveys with all the relevant stakeholders, including physicians, formal and informal caregivers, staff members, and bioengineers, makes the evaluation of the impact of one technological application more effective and ensures that the system meets the quality and sustainability standards for people with AD and those who take care of them [75]. By following a nudge theoretical approach [76], thanks to the collaboration of the Catholic University of the Sacred Heart, Bicocca University, and IRCCS Auxologico Institute in Milan (Italy), we set up the SENIOR (SystEm of Nudge theory based ICT applications for OldeR citizens) project, an advanced technology coaching system able to collect and integrate physiological, psychological, and behavioral data, with the final aim of interacting with community-dwelling senior citizens with MCI and providing them with personalized feedback for maintaining independence from caregivers and improving their lifestyles [77]. Cognitively impaired older adults’ mobility may be reduced due to frailty, sensory impairments, functional limitations, and comorbidities. Digital navigation devices can overcome these deficits, providing a sense of situation-awareness and offering proactive navigational assistance using remote monitoring by physicians and caregivers. A wearable monitoring solution designed for older adults in a continuous, non-invasive way is thus necessary in order to detect SD physiological correlates via the use of digital sensors. According to Ghosh et al. [78], wearables-based sensing of everyday behavior can be used to provide ecologically valid digital biomarkers of AD. In their study, the authors used GPS tracking to measure ecological outdoor behavior in people with AD and showed that they significantly differed from controls in specific mobility domains.

### 1.7. Aim of the Study Protocol

The first endpoint of the research is to explore differences in SN performances among healthy older adults, individuals with SCD, and patients with MCI due to AD on a VR task (i.e., the “AppleGame”) and on a naturalistic task (i.e., the Detour Navigation Test-modified version, DNT-mv) using an innovative technological apparatus recording gait data and revealing physiological parameters that may be associated with SD.

The second endpoint of the research is to verify if examinees’ performances in such a well-characterized laboratory-based SN-testing task may predict impairment in a real-world context.

## 2. Materials and Methods

### 2.1. Design, Study Population, Recruiting Centers and Trial Registration

This is a multi-center prospective observational study. A sample of outpatients with SCD and MCI due to AD will be enrolled from three sites in Lombardy (Italian Region): “San Gerardo” Hospital (Monza), “Luigi Sacco” University Hospital (Milan), and Fondazione IRCSS Ca’ Granda Ospedale Maggiore Policlinico (Milan, Italy).

Individuals with SCD will be detected according to Jessen and colleagues’ criteria [79] while prodromal AD will be defined according to Dubois and colleagues’ criteria [80], respectively. Healthy older adults will be enrolled through advertisements distributed in social centers for senior citizens in Milan (Italy) and through popular science events (conferences, webinars) concerning research in AD prevention. The three sites currently use the neuropsychological batteries reported in the Appendix A. Healthy older adults will be assessed by the experimenters at the Department of Psychology, Catholic University (Milan, Italy), by adopting the same neuropsychological battery as the IRCSS Ca’ Granda Ospedale Maggiore Policlinico (Milan, Italy). Family medical history of AD was collected during clinical interview along with laboratory tests results and neuroimaging findings for outpatients with SCD and MCI due toAD.

For the whole sample, inclusion criteria will involve the following: age from 65 to 85 years; education not less than 5 years; basic ICT skills. All participants will be excluded from the study according to the presence of visual, hearing, or motor impairment significantly interfering with SN tasks; neurological/psychiatric disease or other medical conditions preventing SN; history of alcohol or drugs addiction; intake of psychotropic drugs; and presence of dementia. Recruitment will end on 29 February 2024.

With the aim of obtaining results that can be generalized, sociodemographic and clinical features of the sample to be recruited will be analyzed among the research team members prior to the sample enrollment according to epidemiological studies carried out on the Italian elderly population, specifically including MCI patients [81,82,83] and individuals with SCD [84].

The Uniform Resource Locator for the clinical trial registration is the following one: https://classic.clinicaltrials.gov/ct2/show/NCT05944601 (identifier: NCT05944601) (accessed on 13 July 2023).

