### 2.4. Statistical Analysis

Data distribution will be first checked on collected variables by assessing skewness and kurtosis values, by performing normality and heteroscedasticity tests, and by visually inspecting histogram and Q–Q plots. Based on data meeting or non-linear model assumption, either parametrical or non-parametrical analyses will be performed. By means of the R marco *pwr* [86], the minimal sample size has been set as 76 participant, based on a power analysis for a multiple regression model that took into account the following parameters: α = 0.05; 1-β = 0.9; *f*^2^ = 0.15 (medium effect size, in order to be conservative) [87]; and numbers of predictors: 3 (age, APOE genotypes, and belonging to each group, with the last two predictors as dummy variables).

We will detect the route disorientation scores, i.e., WTs and MsH, as already described in Puthysserypaddy et al. [64]. Accordingly, all the violations in terms of deviations from the pre-established return path (i.e., movement at an intersection onto a different path as compared to the original one, or non-roadable walkways) will be written down by the experimenter as WTs in a pre-set paper grid for *Route A*. The overlaps with the *Route A* return path, and, likewise, non-roadable walkways will be written down by the experimenter as WTs in a pre-set paper grid for Route *B*. Further, we will detect the MsH as the participant either slows down/stops and looks around to aid orientation or verbally admits to the experimenter that he/she is unsure about his/her whereabouts, both for *Route A* and the *Route B* return path.

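### Controls and patients come from different sources, and no stated analysis adjusts for education, so an education gap could be read as a disease effect

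*Protocol article*

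**What the plan says.** Section 2.1 gives two recruitment routes that do not overlap. For the patient groups: "A sample of outpatients with SCD and MCI due to AD will be enrolled from three sites in Lombardy". For the comparators: "Healthy older adults will be enrolled through advertisements distributed in social centers for senior citizens in Milan (Italy"), and also "through popular science events (conferences, webinars) concerning research in AD prevention". No split between the two control routes is given.

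Education and computer familiarity enter the design only as minimum entry requirements for the whole sample: "education not less than 5 years; basic ICT skills". No matching, quota or stratification by education is stated. The same section plans a review of sample characteristics before enrolment, with this purpose: "With the aim of obtaining results that can be generalized, sociodemographic and clinical features of the sample to be recruited will be analyzed". The yardstick is epidemiological work on older Italians.

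Section 2.4 names one set of predictors, in the sentence that justifies the sample size: "numbers of predictors: 3 (age, APOE genotypes, and belonging to each group, with the last two predictors as dummy variables"). Later in that section, gait parameters and the SSNC questionnaire are compared across the three groups by one-way ANOVA or its non-parametric equivalent, with no covariate. No separate model is written out for the group comparison of AppleGame drop errors, wrong turns (WTs) or moments of hesitation (MsH).

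**The concern.** The first endpoint is the difference in navigation between the three groups, and section 3 expects MCI to do worse than controls and SCD. Recruitment source is completely tied to control status: no control comes from a clinic and no patient from an event or social centre. Source itself therefore cannot be adjusted for. Only measured characteristics that differ between sources can be.

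Education is the obvious candidate. It may differ between volunteers and clinic outpatients, it may be related to performance on a computer task and on a route-memory task, and above 5 years nothing in the design limits how far the groups can diverge. If it does differ, part of a control-versus-MCI or control-versus-SCD difference would reflect who was recruited rather than cognitive status. More participants would not shrink that part. The SCD-versus-MCI contrast is less exposed, because both groups come from the same kind of source.

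**Working it through.** **1. Where the article could deal with education**

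| Place | What it does | Does it make the groups comparable on education? |
|---|---|---|
| 2.1, eligibility | 5-year minimum for everyone | No; nothing limits differences above the minimum |
| 2.1, review before enrolment | Sets the sample against epidemiological studies, for generalisability | No; patients and controls could each resemble a published population and still differ from each other |
| 2.4, power sentence | Age, APOE, group | No education term |
| 2.4, ANOVA on gait and SSNC | Group only | No covariates, not even age |

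**2. What an ignored gap would do**

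The article gives no education figures, so two inputs are assumptions:

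- D, the control-minus-MCI gap in education in SD units: 0.5 to 0.8.
- r, the within-group correlation of education with the outcome: 0.2 to 0.3.

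From the article: 25 controls, 26 MCI patients, two-sided α = 0.05.

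With no true group effect, the spurious standardised difference is d = r × D. The rejection rate comes from a noncentral t distribution with 25 + 26 − 2 = 49 df and noncentrality d × √(25 × 26 / 51) = d × 3.570.

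| r | D | d = r × D | Noncentrality | Rejection rate |
|---|---|---|---|---|
| 0.2 | 0.5 | 0.10 | 0.357 | 6.4% |
| 0.3 | 0.5 | 0.15 | 0.536 | 8.2% |
| 0.2 | 0.8 | 0.16 | 0.571 | 8.7% |
| 0.3 | 0.8 | 0.24 | 0.857 | 13.4% |

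A wider grid (D from 0.25 to 1.0, r from 0.1 to 0.4, normal approximation) runs from 5.1% to 29.8%. These are rates per outcome. The test is two-sided, so the rates are the same if the gap runs the other way. In that case a real MCI deficit would be partly hidden rather than inflated.

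**3. What the extra covariate costs in power**

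The article sizes the study with "α = 0.05; 1-β = 0.9" and f² = 0.15. The stated 76 does not reproduce at these inputs. With three predictors the overall F test needs N = 99, and N = 76 gives power 0.796. That is a separate matter and is given here only as the baseline for the cost.

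- *Test of the group effect* (2 df, partial f² = 0.15, noncentrality 0.15 × 76 = 11.4). Age, APOE and two group dummies leave 76 − 4 − 1 = 71 residual df and power 0.8501. Adding education leaves 70 df and power 0.8498.
- *Overall F test at the same total f²*. Going from three to four predictors lowers power from 0.796 to 0.747. This test asks whether all predictors together explain anything, which is not the first-endpoint question.

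**The case against.** The strongest reply is that the predictor list is an input to a power calculation. It is tied to no outcome and is not declared to be the final adjustment set. The article is condensed, and a full analysis plan that is not shown could add education. This stands as a limit: a reader might infer that the plan has fixed age and APOE as the only covariates for drop errors, WTs and MsH, and the article does not say so. What remains is that this is the only predictor set it states, that the study was sized on it, and that the one three-group test it spells out, the ANOVA on gait and the SSNC, adjusts for nothing.

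A second tempting reading is that the bias must favour the hypothesis, because people who attend science events are better schooled and more used to computers than patients. The document does not support this. It gives no education or computer-use data, it recruits controls through social centres as well, it requires basic ICT skills of patients too, and it does not describe the outpatients as a consecutive series. The direction is plausible but not documented.

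Third, the size is assumed. Three of the four scenarios stay below 9%, and only the joint upper corner reaches 13.4%. That is correct, and the range should be read as an illustration.

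Fourth, education stands in only partly for computer practice, so adjustment would not clear the AppleGame comparison of every source effect. That also stands.

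**Conclusion.** The point holds as a possible confounder that the stated analyses leave uncontrolled. It is not a demonstrated bias. The different sources, the education floor without matching, and the absence of education from every stated analysis are all in the text. The review of sample features before enrolment serves external validity and does not make controls comparable with patients.

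If controls and MCI patients differ by 0.5 to 0.8 SD in education, and education correlates 0.2 to 0.3 with the outcome, the false-positive rate for that contrast is about 6% to 13% per outcome instead of 5%. Both inputs are assumptions, and the article fixes neither the size nor the sign of the gap. The change is still worth making: years of education must be established to apply the entry criterion, and adjusting for them costs the group test almost no power.

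**What to change.** - Add years of education beside age and APOE in the three-group analyses of AppleGame drop errors, WTs and MsH.
- Use the same covariates for the gait and SSNC comparisons, in place of an unadjusted one-way ANOVA.
- Report the distribution of education by group.
- Show the unadjusted group estimate next to the adjusted one.
- State as a limitation that education will not fully remove differences in computer practice between the sources.

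The cost is one degree of freedom (power of the group test 0.8501 to 0.8498 at N = 76) and a few sentences in the plan. The main downside is possible over-adjustment: if education itself affects disease risk, the adjusted estimate may lose some of the true group difference. Showing both estimates lets the reader judge this. None of these steps depends on recruitment still being open; the article gives 29 February 2024 as its end.
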